## Abstract

**Background:**

Taurine (Tau) is involved in many biochemical functions such as regulation of glucose and lipid metabolism, enhancement of energy expenditure, anti-inflammatory effects and appetite control. The most important effect of Tau in obesity is its direct effect on adipose tissue. Some evidence has shown an impaired FGF (fibroblast growth factor) 19 and 21 biosyntheses in obesity. Besides the effects of eicosapentaenoic acid on serum FGF concentrations, the effect of other nutrients on FGFs is not clear. Since obesity as an important health problem is rising around the world and on the other side, Tau biosynthesis is reduced by adipose-tissue-derived factors in obesity, the effects of Tau and a weight-loss diet on obesity need to be investigated further.

**Methods:**

We will conduct an 8-week. double-blind, parallel-group, randomized controlled clinical trial to investigate the effect of Tau supplementation on fasting serum levels of FGFs, β-Klotho co-receptor, some biochemical indices and body composition in 50 obese women aged between 18 and 49 years on a weight-loss diet.

**Discussion:**

We will determine the other advantages of a weight-loss diet on new metabolic risk factors. Since Tau may regulate adipose-tissue-derived factors and a weight-loss diet can promote the useful effects of Tau supplementation; for the first time, the effects of a weight-loss diet along with Tau supplementation on these variables will be assessed.

**Trial registration:**

Iran Clinical Trials Registry, ID: IRCT20131125015542N2. Registered on 24 November 2018.

**Electronic supplementary material:**

The online version of this article (10.1186/s13063-019-3421-5) contains supplementary material, which is available to authorized users.

## Introduction

Obesity rates are rising around the world. Since excess body weight is associated with a higher incidence of cardiovascular disease, hyperlipidemia, hypertension, type 2 diabetes mellitus and some cancers, obesity is the fifth cause of mortality all over the world [1, 2]. According to the new studies, some novel obesity-related hormones may have an important role in obesity treatment as metabolic regulators [3].

Fibroblast growth factors (FGFs) 19 and 21 as members of FGFs are different from canonical FGFs. FGF19 and FGF21 could circulate in vessels as hormones. They increase total energy expenditure. Furthermore, they may decrease blood glucose, insulin, triglycerides, fat mass and body weight [4]. FGF19 and FGF21 link to a unique dual receptor complex consisting of β-klotho and activate tyrosine kinase FGF receptors (FGFR1–4) via a low-affinity interaction with heparan sulfate glycosaminoglycans (HSGAGs). β-klotho links to those and facilitates FGFR activation. β-klotho mainly expresses in metabolic organs including liver, adipose tissue and pancreas [5, 6].

Some evidence has shown that FGF19 (released by the intestine) and FGF21 (released by the liver and adipose tissue) play an important role in glucose and lipid metabolism. Some evidence has also shown an impaired FGF19 and 21 biosyntheses in obesity [7]. According to the result of a cross-sectional study, the serum level of FGF21 and FGF19 was high and low in the obese subjects, respectively. Furthermore, β-klotho gene expression was decreased. Adipose-derived pro-inflammatory factors could decrease gene expression of β-klotho in obesity. Since the function of FGF19 and FGF21 is dependent on β-klotho as a co-receptor; decreased expression of β-klotho causes metabolic disorders [8]. Thus, β-klotho co-receptor has been considered as a new marker in metabolic diseases [9, 10]. Since β-klotho expression is affected by adipose-derived pro-inflammatory factors, weight loss could be effective in reduction of resistance to FGF21 and β-Klotho co-receptor up-regulation.

Adiponectin has an important role in glycemic and lipid homeostasis. Recent evidence has shown that FGF21 increases adiponectin expression [7]. Generally, the serum level of FGF21 is directly associated with insulin resistance and increases liver stress markers in obese individuals. In addition, the serum level of FGF19 is reversely associated with insulin sensitivity and improvement in lipid metabolism. It seems that these two FGFs overlap in the body metabolism function [8]. Although one study showed the increasing effect of eicosapentaenoic acid (EPA) on serum FGF21 [11], the effect of other nutrients on FGFs is not clear.

Taurine (2-aminoethanesulfonic acid, Tau) is a sulfur-containing amino acid that is synthesized endogenously from cysteine (Cys) or methionine (Met). Additionally, this amino acid could be provided by diet, especially seafood. Diet-derived Tau is carried in the blood circulation in a low amount to other tissues [12]. There is some evidence that shows that the serum level of Tau is reduced in obesity [13, 14]. Tau is involved in many biochemical functions such as regulation of glucose and lipid metabolism, enhancement of energy expenditure, anti-inflammatory effects and appetite control. The most important effect of Tau in obesity is its direct effect on adipose tissue [12]. Tau increases genes expression that is related to energy expenditure including peroxisome proliferator-activated receptor (PPAR) α, PPAR γ and PPAR γ co-activator protein (PGC)-1α. Thus, this amino acid increases energy expenditure in the white adipose tissue. In the other side, Tau induces PGC-1α gene expression in the brown adipose tissue [15]. Also, in adipose tissue, it decreases the number of M1 macrophages (secreting pro-inflammatory cytokines and reactive oxygen species (ROS)) and increases the number of M2 macrophages (involved in the clearance of free fatty acid (FFA) and inhibition of lipotoxicity). Hence, Tau could reduce inflammatory markers such as high-sensitivity C-reactive protein (hs-CRP) [12, 15]. Also, this amino acid is anti-inflammatory and anti-oxidant through its sulfonic acid group and non-participation in protein structure (in free-form) [16]. Although the result of studies is controversial, there is some evidence that shows the beneficial effect of Tau on energy expenditure, weight and body composition in obesity and diabetes in both animals and humans [15]. Tau has a putative role in increasing energy expenditure, fatty acid β-oxidation and adipose tissue hypertrophy reduction [15]. Since serum FGF concentration is associated with visceral obesity [7] and the effect of Tau supplementation on serum FGF concentration is not clear, we decided to conduct a randomized controlled clinical trial (RCT) investigating the effect of Tau supplementation on fasting serum levels of fibroblast growth factors (FGF19, FGF21), β-Klotho co-receptor, some of the metabolic risk factors and body composition in obese women on a weight-loss diet.

### Hypothesis and aims

We hypothesize that Tau supplementation along with a standard weight-loss diet improves serum levels of biochemical parameters and body composition. The primary aims of the present RCT are the assessment of Tau supplementation on fasting serum levels of biochemical parameters and body composition. Furthermore, the secondary aims will evaluate the associations between changes in concentrations of fibroblast growth factors (FGF19, FGF21) and β-Klotho co-receptor with other variables.

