### Sample size

The sample size was calculated based on the effect of Tau supplementation on changes in hs-CRP in obese people that was conducted by Rosa et al. [12]. It was computed by considering 95% confidence interval and 80% power (α = 0.05 and β = 0.2). In addition, the mean and standard deviation (SD) of hs-CRP levels in the mentioned study was as follows: μ_1_ = 14.30; μ_2_ = 10.50; SD_1_ = 2.90; SD_2_ = 2.40. We considered a 20% attrition rate. Finally, 25 subjects are considered for each group. All individuals will be included in the RCT if they meet the inclusion criteria and are willing to participate in the study to achieve the estimated sample size.

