### Measurements

An individual information questionnaire including demographic situations, history of diseases, supplementations and medications will be filled at the baseline. Dietary intake will be evaluated by 3-day 24-h recall questionnaires (two weekdays and one weekend day) at the beginning, middle and the end of the study. Total calorie and macroniutrients intake will be calculated using Nut IV (the Hearst Corporation, San Bruno, CA, USA ). The participants will be asked not to change their physical activity level (PAL). Physical activity levels will be assessed by the International Physical Activity Questionnaire (IPAQ) at the beginning and end of the study. The physical and anthropometric measurements will be given with minimal clothing and without shoes. Body weight will be measured using a 100-g accuracy scale (Seca). Height will be measured using a 0.5-cm accuracy Seca stadiometer. BMI will be computed by dividing body weight (kg) to the square of height (m). Waist circumference will be measured using a tape meter at the midpoint between the lowest rib and iliac crest and at the end of a normal expiration to the nearest 0.5 cm. A TANITA BC-418 body analyzer will be applied to estimate total body fat, fat percent, fat-free mass and fat-free mass percent. Five milliliters of venous blood sample (in a regular tube) will be taken after a 10–12-h overnight fast at the baseline and end of the study. Blood samples will be centrifuged at 1500 g for 15–20 min to separate the serum. Serum will be stored at − 80 °C and will be used for biochemical analysis, such as FGF19 (μg/mL), FGF21 (μg/mL), β-klotho co-receptor (μg/mL), leptin (μg/mL), adiponectin (μg/mL), hs-CRP (μg/mL), insulin (μU/mL), fasting blood sugar (FBS) (mg/dL), total cholesterol (TC), high-density lipoprotein (HDL-C), triglyceride (TG), alanine transferase (ALT), aspartate transaminase (AST) and gamma-glutamyl transferase (GGT), in the serum. Enzyme-linked immunosorbent assay (ELISA) kits will be applied to measure serum FGFs, β-klotho co-receptor, leptin, adiponectin, hs-CRP and insulin, lipid profile and serum glucose concentration. Also, serum hepatic enzymes will be measured using the enzymatic method by Pars Azmoon kits (Tehran, Iran). Low-density lipoprotein (LDL-C) concentrations will be computed by the Friedewald equation. Homeostasis model assessment – insulin resistance (HOMA-IR) will be calculated as follows:$$ \mathrm{FBS}\ \left(\mathrm{mg}/\mathrm{dL}\right)\times \mathrm{fasting}\ \mathrm{serum}\ \mathrm{insulin}\ \left(\mu \mathrm{U}/\mathrm{mL}\right)/405, $$

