### Statistical analysis

We will use intention-to-treat (ITT) and per-protocol (PP) populations in the analysis. The ITT population consists of all individuals who will be randomized, whereas the PP population consists all participants who complete the 8-week intervention. The data will be revised randomly to check accuracy and completeness. All data will be reported as mean ± SD. The percentage changes for each variable will be computed by the following formula:$$ \left[\left(E-B\right)/\mathrm{B}\times 100\right], $$

where *E* and *B* are the end value and the baseline value of variable, respectively. The data normality will be analyzed using the Kolmogorov-Smirnov test. To compare parametric continuous data between and within the groups, the independent sample *t* test and the paired sample *t* test will be used, respectively. In addition, to compare the differences in asymmetric variables between and within the groups, the Mann-Whitney test and Wilcoxon test will be applied, respectively. The analysis of covariance (ANCOVA) test will be used to control confounding variables. To evaluate the association between changes in fibroblast growth factors (FGF19, FGF21), β-Klotho co-receptor concentrations and other variables, linear regression models will be used. SPSS version 21 (IBM, Armonk, NY, USA) will be used for data analysis. A *p* value < 0.05 will be considered statistically significant.

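### The primary aims take in some 20 to 23 between-arm comparisons, each at p < 0.05, while the trial is sized on hs-CRP, which is never named as primary

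*Protocol article*

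**What the plan says.** Under Hypothesis and aims, the article states: "The primary aims of the present RCT are the assessment of Tau supplementation on fasting serum levels of biochemical parameters and body composition". It continues that "the secondary aims will evaluate the associations between changes in concentrations of fibroblast growth factors (FGF19, FGF21) and β-Klotho co-receptor with other variables". No treatment comparison is placed at the secondary level.

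The Measurements section supplies the variables:

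- By immunoassay: "Enzyme-linked immunosorbent assay (ELISA) kits will be applied to measure serum FGFs, β-klotho co-receptor, leptin, adiponectin, hs-CRP and insulin". Fasting glucose belongs with these.
- Lipids and liver enzymes: "total cholesterol (TC), high-density lipoprotein (HDL-C), triglyceride (TG), alanine transferase (ALT), aspartate transaminase (AST) and gamma-glutamyl transferase (GGT").
- Two derived serum variables: "Low-density lipoprotein (LDL-C) concentrations will be computed by the Friedewald equation", and "Homeostasis model assessment – insulin resistance (HOMA-IR) will be calculated as follows", the latter from glucose and insulin.
- Four body-analyzer variables: total fat, fat percent, fat-free mass and fat-free-mass percent.
- Weight, BMI and waist circumference, described as anthropometric measurements.

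The Statistical analysis section names the between-group tests (t test or Mann-Whitney, with ANCOVA for confounders) and two analysis populations. It ends with one threshold for everything: a p "value < 0.05 will be considered statistically significant".

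The Sample size section says: "The sample size was calculated based on the effect of Tau supplementation on changes in hs-CRP in obese people". No section designates hs-CRP as the primary outcome. The abstract and the end of the introduction list the FGFs and β-Klotho first.

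**The concern.** The hypothesis is that taurine improves the biochemical parameters and body composition. The article gives no rule for what would confirm it. With a primary class of 20 or more variables and a flat 5% threshold, any one nominally significant difference could be presented as a result on the primary aim. The 5% then applies to each test and not to the trial's main conclusion.

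The sizing adds to the difficulty. The one variable with a stated effect and power is not identified as decisive, and the variables given most prominence were not sized. A reader cannot tell from the article which result decides the trial.

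**Working it through.** **Count of primary comparisons (Measurements section)**

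- Serum, measured: FGF19, FGF21, β-Klotho, leptin, adiponectin, hs-CRP, insulin, glucose, TC, HDL-C, TG, ALT, AST, GGT = 14.
- Serum, derived: LDL-C and HOMA-IR, giving 14 + 2 = 16.
- Body analyzer: 4, giving 20.
- Weight, BMI and waist, if read as body composition: 3, giving 23.

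**The plan's own figures.** The article states no family-wise error rate, so there is none to reproduce. Its stated sample size is 25 per group. The hs-CRP inputs are a difference of 14.30 − 10.50 = 3.80 and SDs of 2.90 and 2.40. The pooled SD is √((2.90² + 2.40²)/2) = 2.66, so d = 3.80/2.66 = 1.43. At two-sided 5% and 80% power this needs 8 per group by the normal formula or 9 by the t test. Allowing for 20% attrition gives 8/0.8 = 10, or 9/0.8 = 11.25, rounded up to 12. The stated 25 is not reproduced. That is a separate matter and does not affect what follows.

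**Independent tests, no true effect on any outcome.** P(at least one p < 0.05) = 1 − 0.95^m.

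- m = 16: 56.0%
- m = 20: 64.2%
- m = 23: 69.3%

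The expected number of false positives is 23 × 0.05 = 1.15, whatever the correlation.

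**Correlated tests.** The article gives no correlations, so these are assumptions. With a common correlation r, each test statistic is √r·U + √(1−r)·E, where U is a standard normal variable shared by all tests and E is a standard normal variable specific to each test. For m = 23, the chance of at least one significant result is:

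| r | Two-sided, either direction | Favourable direction only |
|---|---|---|
| 0 | 69% | 44% |
| 0.1 | 67% | 39% |
| 0.3 | 58% | 30% |
| 0.4 | 52% | 26% |
| 0.5 | 45% | 22% |
| 0.7 | 31% | 15% |

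The favourable-direction column uses 0.025 per test; at r = 0 it is 1 − 0.975^23 = 44.1%. For 20 outcomes it is 1 − 0.975^20 = 39.7%.

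Two block structures were also simulated. They set high correlation (0.6 to 0.95) among the body measures and among related laboratory variables, and 0 to 0.5 elsewhere. The two-sided rate was between 39% and 59%.

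**Near-duplicates.** With height fixed, BMI = weight/height², so the percentage change in BMI equals the percentage change in weight. Absolute changes differ, because height varies between women. Fat-free-mass percent is 100 minus fat percent, so absolute changes mirror each other, but percentage changes do not, because the denominators differ. On neither scale are both pairs exact copies. Overlap of this kind lowers the family-wise rate but lets one chance difference show up as two findings.

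**Power.** Twenty completers per arm is 25 × 0.8. For an unsized outcome, a two-sided 5% t test then has 80% power at d of about 0.91. For the stated hs-CRP effect (d = 1.43), power is about 99% at 5%. At the Bonferroni level 0.05/23 = 0.0022 it is about 88%, by the t test.

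**The case against.** The strongest reply is that this is a condensed article. Endpoint hierarchy and multiplicity handling often sit in a full protocol or analysis plan, and neither is at hand. The trial is also registered, and the registry entry cannot be seen here. The article speaks of aims; it does not say that each variable is an endpoint or that one small p value establishes efficacy. This stands to the extent that the absence of a multiplicity method is not in itself a fault. It does not remove the point, because the article states that the primary aim is the whole class, that the secondary aims are associations only, and that 0.05 applies throughout.

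A reader might infer that at least one false primary success is more likely than not. The documents do not support that as a fact. It requires no effect on any outcome, two-sided counting in either direction, and weak correlation; the rate falls below 50% a little above r = 0.4. The hypothesis concerns improvement, so a significant difference in the harmful direction would not confirm it. In the favourable direction the rate stays at or below about 44% for independent or positively correlated tests.

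The count is also open to reading. The article treats weight, BMI and waist as anthropometry, which supports 20 as much as 23. LDL-C and HOMA-IR are functions of other listed variables. A reader might further infer that two outcomes are exact copies of two others, but that holds for only one pair on any given scale.

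Finally, hs-CRP is not the only defensible primary. A multiple-primary design with adjustment is equally valid.

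**Conclusion.** The point holds in measured form. Followed as written, the article runs 20 to 23 primary between-arm comparisons at an unadjusted 5% each, and the variable used for sizing is not named as primary. With no true effect, the chance of at least one nominally significant primary result is up to about 69%, and roughly 40 to 65% under assumed moderate correlation. In the favourable direction only, it is at most about 44%, and about 30% at r = 0.3.

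These figures assume no effect on any outcome, one test per outcome, correlations that are zero or positive, and an agreed favourable direction for every variable. Analysing two populations, and using both unadjusted tests and ANCOVA, could raise the rates further; this was not quantified. The conclusion does not depend on the exact correlation. Even at r = 0.7 the two-sided rate is 31%, about six times nominal, and the favourable-direction rate is 15% against 2.5% for a single test.

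**What to change.** Before unblinding, take one of two routes.

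1. Name one primary outcome and one between-arm comparison. hs-CRP at 8 weeks is the natural candidate, as the only variable sized. If an FGF is preferred, restate the detectable effect for it: about d = 0.91 at 80% power with 20 completers per arm. Make the other variables secondary, and either adjust them with Holm or Benjamini-Hochberg or report them as exploratory.
2. Keep several primaries, list them explicitly, and control the family-wise rate with Holm. The stated hs-CRP effect remains well powered, since Holm is never less powerful than Bonferroni. For the other outcomes the detectable effect should be restated at the adjusted level.

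Either route takes a few sentences in the aims and statistical analysis sections and no extra participants for hs-CRP. The downside is fewer nominally significant results. Whether to drop BMI or fat-free-mass percent as separate test outcomes is a matter of preference; it is enough to report each overlapping pair as one finding.

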## Methods

### Design and setting

We will be performed a double-blind, parallel-group, clinical RCT. The proposed RCT will be conducted at the Private Nutrition Therapy Clinics in Ahvaz for 8 weeks to evaluate the effect of daily 3-g Tau supplementation in obese individuals Fig. 1. (The Standard Protocol Items: Recommendations for Interventional Trials (SPIRIT) 2013 Statement will be followed in this trial (Additional file 1)). Figure 1 shows the Flow diagram of the study.

**Fig. 1 Fig1:**
[figure not shown]
Flow diagram of the study

### Participants

Participants will be 50 non-menopause obese women. Inclusion criteria will be included women aged 18 to 49 years old; body mass index (BMI) range between 30 and 40 kg/m^2^; exclusion criteria will be included: menopause, pregnancy and lactation; having a history of food allergy, cancer, acute or chronic renal failure, acute or chronic hepatic failure, thyroid disorders, gastrointestinal diseases, taking multivitamin/mineral supplements, taking herbal supplements or weight-loss drugs, surgery for weight loss and any weight loss over the past 6 months.

### Ethics and trial registration

The eligible participants will be notified about the study protocol. The protocol is approved by the Ethics Committee of Ahvaz Jundishapur University of Medical Sciences that is in accordance with the Declaration of Helsinki (approval number: IR.AJUMS.REC.1397.590). Each participant will sign an informed consent form. All collected data will be held confidential. This study is registered with the Iranian Registry of Clinical Trials (registration number: IRCT20131125015542N2).

### Sample size

The sample size was calculated based on the effect of Tau supplementation on changes in hs-CRP in obese people that was conducted by Rosa et al. [12]. It was computed by considering 95% confidence interval and 80% power (α = 0.05 and β = 0.2). In addition, the mean and standard deviation (SD) of hs-CRP levels in the mentioned study was as follows: μ_1_ = 14.30; μ_2_ = 10.50; SD_1_ = 2.90; SD_2_ = 2.40. We considered a 20% attrition rate. Finally, 25 subjects are considered for each group. All individuals will be included in the RCT if they meet the inclusion criteria and are willing to participate in the study to achieve the estimated sample size.

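### Read as a two-arm comparison, the stated sample-size inputs need 10 to 12 women enrolled per group, so 25 does not follow from them; the mismatch is on the safe side

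*Protocol article*

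**What the plan says.** The whole justification is in the Sample size section of the protocol article. The basis is a previous taurine study: "The sample size was calculated based on the effect of Tau supplementation on changes in hs-CRP in obese people". The error rates are given as "It was computed by considering 95% confidence interval and 80% power (α = 0.05 and β = 0.2". The planning values are "μ_1_ = 14.30; μ_2_ = 10.50" and "SD_1_ = 2.90; SD_2_ = 2.40", which the section describes as the mean and SD of hs-CRP levels in that study. The result follows directly: "We considered a 20% attrition rate. Finally, 25 subjects are considered for each group".

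The section gives no n before attrition, no formula and no sidedness for alpha. It names no second endpoint, multiplicity allowance or deliberate rounding up. Its closing sentence treats 25 per group as the estimated size. The Randomization and blinding section repeats 25 per arm. The Statistical analysis section plans an independent-sample t test between groups, with the Mann-Whitney test for asymmetric variables.

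**The concern.** Every number needed for a standard two-sample calculation is printed, and so is the result, but the result does not follow from the inputs. The planning difference is 3.80 against SDs below 3, a very large standardised effect, and an effect of that size needs far fewer than 25 per group at 80% power.

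There is a second difficulty. The calculation is said to rest on changes in hs-CRP, yet the figures are called levels. The section does not say whether 14.30 and 10.50 are the values in two arms or the values before and after in one arm. This matters because both arms here follow the weight-loss diet and the planned comparison is between arms. A pre/post fall in one arm is not the effect that this comparison estimates.

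What is at stake is the meaning of the power statement. A reader will take 25 per group as the number that gives 80% power for the cited effect. It is not, and the difference that 25 per group does detect at 80% power is nowhere stated.

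**Working it through.** **Inputs** (all from Sample size): means 14.30 and 10.50; SDs 2.90 and 2.40; alpha 0.05; power 80%; attrition 20%. Assumptions: two-sided alpha, equal allocation (25 and 25 in Randomization and blinding), and the two means read as two arms.

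**Step 1. Effect size.**
- Difference: 14.30 − 10.50 = 3.80
- Sum of variances: 2.90² + 2.40² = 8.41 + 5.76 = 14.17
- Pooled SD: √(14.17/2) = 2.66
- Standardised difference: 3.80/2.66 = 1.43

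**Step 2. Attempt to reproduce 25.** Normal formula:

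n = (1.960 + 0.842)² × 14.17 / 3.80² = 7.849 × 14.17 / 14.44 = 7.70, so 8 per group.

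By the t test, n = 8 gives 75.7% power and n = 9 gives 81.1%, so 9 per group.

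Attrition: 8/0.8 = 10; 9/0.8 = 11.25, so 12. The inputs give 10 to 12 enrolled per group, not 25.

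**Step 3. Does another reading at 80% power give 25?**

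| Variant | Completers per group | Enrolled per group |
|---|---|---|
| One-sided alpha | 7 | 9 |
| SD 2.40 only | 7 | 9 |
| SD 2.90 only | 10 | 13 |
| t test with worst-case Mann-Whitney efficiency (9/0.864) | 11 | 14 |
| Bonferroni for 25 endpoints | 16 | 20 |
| SD of change 3.76 (correlation 0), normal formula | 16 | 20 |
| SD of change 3.76 (correlation 0), t test | 17 | 22 |
| SD of change with correlation 0.5 (2.69) | 8 | 10 |
| The two SDs added (5.30) | 31 | 39 |

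The SD of change is built from the two printed SDs as √(2.90² + 2.40² − 2r × 2.90 × 2.40); at r = 0 it is √14.17 = 3.76. None of these gives 25. Raising power to 99% comes close (19 completers and 24 enrolled by the normal formula; 20 and 25 by the t test), but that contradicts the stated "80% power (α = 0.05 and β = 0.2".

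**Step 4. What 25 per group delivers.** With 20% attrition, 25 × 0.8 = 20 completers per group. Power by the t test for a difference of 3.80:

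| Reading | 20 per group | 25 per group |
|---|---|---|
| Two arms, SD 2.66 | 99.3% | 99.9% |
| Pre/post, SD of change 3.76 | 87.5% | 93.8% |

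**Step 5. Difference detectable at 80% power** (t test, two-sided 0.05):
- 20 per group: 0.91 SD, which is 2.42 hs-CRP units at SD 2.66
- 25 per group: 0.81 SD, which is 2.15 units at SD 2.66

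**The case against.** The strongest reply is that the discrepancy harms nothing. Enrolling more than the inputs require means that the 80% is met and exceeded for the cited difference. Enrolment, allocation, conduct and analysis need no change. This stands, and it is why the point concerns the justification and not the design. A reader might infer from the mismatch that the trial is underpowered; on the section's own assumption it is not.

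A second reply is that the size of the gap depends on a reading that the article leaves open and that only the cited study could settle. This also stands. If the means are pre/post values and the SD of change is 3.76, the need rises to 17 completers, or 22 enrolled. Adding worst-case Mann-Whitney efficiency to that (17/0.864 = 19.7, so 20) gives 20/0.8 = 25 exactly. But this stacks a zero correlation and a worst-case efficiency, neither of which the article mentions, so it cannot be taken as the method used. It shows that the gap may be smaller than the two-arm reading suggests, not that the printed figure was derived this way.

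A reader might also infer that a null result could not be interpreted. That does not follow. A null result is read from the estimate and its confidence interval, whatever the planning paragraph says. Nor can the trial be faulted for low power against some moderate effect, because the article names no such target.

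Finally, a condensed article may leave detail to a fuller protocol. That would excuse a missing formula. It does not cover a printed result that fails to follow from the printed inputs.

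**Conclusion.** The paragraph is wrong as written and should be fixed. Read as a two-arm comparison with two-sided alpha 0.05 and 80% power, its inputs require 8 to 9 completers per group, or 10 to 12 enrolled, against the stated 25. The error is conservative: power for a difference of 3.80 is about 99%, not 80%.

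The conclusion rests on two assumptions. Two-sided alpha is one, and a one-sided test would only widen the gap. The two-arm reading of the means is the other, and it affects the size: under the zero-correlation pre/post reading the shortfall in explanation is 22 against 25. If the means are in fact pre/post values from one arm, the more basic problem is that 3.80 is not the between-arm difference that this trial compares, and its power for that difference is then not established by this paragraph.

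The documents do not support any claim that the trial is too small for its cited effect.

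**What to change.** Keep 25 per group and rewrite the Sample size paragraph to do three things.

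1. Say whether 14.30 and 10.50 are values in two arms or before and after in one arm. If they are pre/post, redo the calculation from the between-arm difference in change and the SD of that change.
2. Give the n that the inputs produce, with test and sidedness. On the two-arm reading this is 8 to 9 completers per group, or 10 to 12 enrolled. Then say why 25 was chosen.
3. State what 25 per group detects at 80% power: a between-arm difference of about 0.91 SD with 20 completers per group (about 2.4 hs-CRP units at SD 2.66), or about 0.81 SD if all 25 are analysed (about 2.2 units).

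The cost is one corrected paragraph. No participants are added and the planned analysis does not change. If the means prove to be pre/post, one further calculation is needed, with a between-arm difference in change and an SD that the article does not now supply.
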